50

51   **Methods/Design:** We designed a pragmatic randomized controlled trial to evaluate the effectiveness of  
52   patient-specific, evidence-based reminders generated at the point-of-care by a multi-specialty decision  
53   support system on clinical practice and the quality of care. We will include all the patients admitted to  
54   the internal medicine department of one large general hospital. The primary outcome is the rate at  
55   which medical problems, which are detected by the decision support software and reported through the  
56   reminders, are resolved (i.e. resolution rates). Secondary outcomes are resolution rates for reminders  
57   specific to venous thromboembolism (VTE) prevention, in-hospital all causes and VTE-related  
58   mortality, and the length of hospital stay during the study period.

59

60   **Discussion:** The adoption of CDSSs is likely to increase across healthcare systems due to growing  
61   concerns about the quality of medical care and discrepancy between real and ideal practice, continuous  
62   demands for a meaningful use of health information technology, and the increasing use of and  
63   familiarity with advanced technology among new generations of physicians. The results of our study  
64   will contribute to the current understanding of the effectiveness of CDSSs in primary care and hospital  
65   settings, thereby informing future research and health care policy questions related to the feasibility and

66 value of CDSS use in health care systems. This trial is seconded by a specialty trial randomizing  
67 patients in an oncology setting (ONCO-CODES, ClinicalTrials.gov: NCT02645357).

68

69 ***Trial registration:*** ClinicalTrials.gov: NCT02577198

70

71 **Keywords**

72 Computerized decision support systems, electronic health records, evidence-based medicine, pragmatic  
73 trial, randomized controlled trial, reminder systems.

74

75

76

77

## 78    **Background**

79

### 80    *Background and rationale*

81    Despite the proliferation of clinical guidelines and continued efforts by local and national health care  
82    systems to optimize decision-making on patient diagnosis, treatment, and management, the quality of  
83    medical care is variable and often suboptimal [1]. There remains an apparent discrepancy between the  
84    growing availability of scientific evidence and the application of this evidence into medical care [2,3].  
85    Non-adherence to evidence-based guidelines, medical errors, and omissions in everyday practice may  
86    occur because of time pressure, inexperience, reliance on memory, multitasking, and failures in  
87    healthcare team coordination.

88    Computerized decision support systems (CDSSs) are information technology-based software that  
89    provide health professionals with actionable, patient-specific recommendations or guidelines for  
90    clinical care at the point-of-care; these messages are intelligently filtered and presented at appropriate  
91    times during the decision-making process in order to enhance patients' health [4,5]. The opportunity to  
92    improve patient care by increasing clinicians' accessibility to medical knowledge at the site of practice  
93    represents one of the main incentives for investing in the development and evaluation of these  
94    sophisticated information systems.

95    In particular, studies focusing on the effectiveness of "new generation" CDSSs demonstrate their  
96    potential to assist with problems raised in clinical practice, decrease the rate of medication errors,  
97    increase clinicians' adherence to guideline- or protocol-based care, and, ultimately, improve the overall  
98    efficiency and quality of health care delivery systems [6-19]. These innovative systems can be  
99    integrated into hospital electronic health records (EHRs) and feature authoritative point-of-care  
100    information services and evidence-based knowledge [20].

101 This has led to some early work: a systematic review assessing the effectiveness of such “new  
102 generation” CDSSs demonstrated encouraging results [21]. Although this review did not show CDSSs  
103 to affect mortality, they were shown to moderately improve morbidity outcomes. Differences were  
104 further observed for costs and health services utilization, but these were often inconsistent in the  
105 direction of effect and small in magnitude. The conclusion of a landmark paper, published nearly 15  
106 years ago, still reflects the current scenario: “*Although the promise of clinical decision support system-  
107 facilitated evidence-based medicine is strong, substantial work remains to be done to realize the  
108 potential benefits*” [22].

109 Current research on CDSSs suffers two noteworthy limitations [5]. First, while numerous studies have  
110 evaluated the effectiveness of CDSSs, comparatively few implemented a randomized controlled trial  
111 (RCT) design. Second, most published evaluations of the impact of CDSSs on health care quality were  
112 conducted in academic medical centers using “homegrown” systems that featured restricted clinical  
113 content for particular conditions (e.g., thromboprophylaxis). There is limited research on “mature”  
114 CDSSs that are commercially available and capable of supporting a wide range of clinical activities.  
115 Across countries, the adoption of these systems by hospitals is likely to increase in the future.

116

### 117 ***Objective***

118 Our study aims to evaluate the effectiveness of patient-specific, point-of-care reminders generated by  
119 the Medilog Decision Support System (MediDSS) [23] on clinical practice and the quality of care in a  
120 general hospital.

121

### 122 ***Methods/Design***

123 This protocol is reported in accordance with the SPIRIT 2013 guidance for content of clinical trial  
124 protocols [24,25].

125    ***Trial design***

126    The CODES (COMputerized DEcision Support) trial will implement a pragmatic, parallel group, and  
127    randomized controlled design with 1:1 allocation ratio. The flow diagram of the study can be found in  
128    Figure 1.

130    ***Study setting***

131    The study will involve the medical staff of the internal medicine departments of the Vimercate Hospital  
132    from Azienda Ospedaliera di Desio e Vimercate (AODV) a multi-site hospital system located in the  
133    Lombardy region of Italy [26]. AODV includes hospitals and health units distributed in the Province of  
134    Monza and Brianza, which covers a population of approximately 850,000 inhabitants. The Vimercate  
135    Hospital has a medical staff of more than 230 doctors, a total of over 900 health professionals, and an  
136    overall capacity of 489 beds. It supports over 20 specialties and subspecialties. The catchment  
137    population is approximately 200,000 inhabitants, with more than 15,000 admissions per year. In  
138    addition to the in-patient wards, the hospital houses many facilities for diagnosis and treatment.  
139    Since 2010, the Vimercate Hospital has been electronically tracking all clinical and administrative  
140    information through an EHR system based on the "*Tabula Clinica*" platform (developed by Dedalus  
141    S.p.A.) [27].

143    ***Eligibility criteria and recruitment***

144    As a pragmatic clinical trial [28,29], CODES seeks to investigate the effectiveness of MediDSS  
145    reminders in everyday clinical practice with diverse patients and varying conditions. Thus, we will  
146    enroll all of the patients admitted into the internal medicine departments of the AODV, without  
147    applying any exclusion criteria.

148

149    ***Intervention***

150    We selected the Mediloggy Decision Support System (MediDSS) after a comparative assessment of  
151    available editorial products using a predefined set of essential criteria [30,31]. MediDSS is a product by  
152    Mediloggy, an Italian developer of scientific software and medical technology. Mediloggy translated and  
153    adapted Evidence-Based Medicine electronic Decision Support (EBMeDS) [32], a CDSS developed by  
154    Duodecim Medical Publications Ltd., a company owned by the Finnish Medical Society Duodecim.  
155    EBMeDS can be described as a set of rules (scripts) based on EBM guidelines and applied to structured  
156    health data. MediDSS further includes knowledge from Swedish, Finnish, INteraction X-referencing  
157    (SFINX), a drug-drug interaction database containing concise evidence-based information about the  
158    harms and benefits of about 18,000 drug interactions and adverse events [33].

159    MediDSS may be used as a stand-alone application, or may integrate structured patient data from EHR  
160    to generate patient-specific reminders, therapeutic suggestions, and diagnosis-specific links to full-text  
161    guidelines. Reminders are automatically generated and displayed on the monitors of clinicians when  
162    they open a patient's EHR, enter a new diagnosis, prescribe a drug, or when new laboratory test results  
163    are available. Reminders were formed using international evidence-based guidelines and subsequently  
164    approved by an international panel of experts. Our study will use international reminders (n=262) that  
165    cover a large number of health conditions across specialties and are derived from the EBMeDS and  
166    SFINX database. In addition, 17 local reminders have been carefully selected by a team of doctors at  
167    Vimercate hospital, along with members of the trial team. Table 1 reports some examples of the  
168    reminders. Figures 2 and 3 show a snapshot of the activation button and of the actual reminders.

169

170    MediDSS reminders will be shown on the EHR of patients only within the intervention group. During  
171    the care of control group patients, the generated reminders will not be shown to the physicians, such  
172    that the control is usual clinical practice without the use of the MediDSS service. However, physicians

173 in both groups will have access to the best evidence for usual care at all times during the trial through  
174 the active searching of full-text EBM guidelines on Internet. All participating physicians will be  
175 informed on the availability and use of the MediDSS system.

176

### 177 *Stepped wedge implementation*

178 The intervention is a new technology: its integration in the current hospital system requires the  
179 configuration and customization of the software. To allow security controls and successful  
180 implementation, the CDSS will be sequentially rolled out to participants over a number of time periods.  
181 We anticipate that the number of periods will be limited (i.e. two or three periods). Over an initial  
182 period, all participants will receive the intervention. The order in which participants will receive the  
183 intervention is not determined at random, but will be determined by selecting physicians prone to  
184 provide constructive feedback to the implementation team. The RCT adopts a stepped wedge  
185 implementation of the intervention, but not a stepped wedge design [34]. Sequential roll-out of the  
186 intervention will not be considered a pilot phase of the trial, but a part of the whole RCT.

187

### 188 *Selection and development of priority reminders*

189 In order to encourage the participation of the hospital staff within the study, we invited hospital  
190 representatives to assess the priority needs of the hospital wards and develop a set of reminders to  
191 address them. One topic of particular interest to the hospitals involved venous thromboembolism  
192 (VTE) prevention. The rationale for the prioritization of this condition is provided below:

193 (i) Despite evidence supporting the benefits of VTE prophylaxis based on the risk stratification process  
194 [35] as well as the availability of local hospital guidelines, the prophylactic drugs were inconsistently  
195 administered among patients.

196 (ii) The Hospital of Vimercate has an increasingly large population of elderly (aged > 65 years old) and  
 197 very elderly (aged > 80 years old) subjects, who have a higher risk of recurrent VTE and acute  
 198 pulmonary embolism [36].

199 (iii) Between 2010 and 2012, 45 patients (9.6%, 95% CI: 7.2–12.6) and 75 patients (16.0%, 95% CI:  
 200 12.9–19.5) died, respectively, within 30 days and 90 days after discharge due to VTE [36].

201 (iv) Research has shown the use of CDSSs to improve the assessment of patients' risk for VTE,  
 202 facilitate appropriate administration of prophylaxis interventions, and reduce the rate of symptomatic  
 203 VTE in hospitalized patients [37-53].

204

205 In order to develop the set of reminders for VTE prevention, the local hospital expert group proposed a  
 206 risk stratification process based on the Padua Score [54]. This formula calculates the overall risk (low  
 207 or high) of VTE for each patient using both clinical and surgical risk factors. Details of the underlying  
 208 algorithm are provided in Box 1.

209

210 Besides the VTE prevention therapy reminders, other scripts were chosen for development and tailored  
 211 to the hospital's needs. The following alerts were identified by the hospital's clinicians as of special  
 212 interest:

- 213 – Adjusting warfarin dose in atrial fibrillation,
- 214 – Alert on heparin-induced thrombocytopenia,
- 215 – Clopidogrel, prasugrel or ticagrelor and aspirin in acute ST-segment elevation myocardial infarction
- 216 (STEMI),
- 217 – Low-molecular-weight heparin as anticoagulant for patients with venous thromboembolism and
- 218 cancer,
- 219 – Selection of antithrombotic therapy in atrial fibrillation on the basis of the CHA2DS2VASc score,

- 220 – Supplementary laboratory measurements in warfarin therapy,
- 221 – Low-dose aspirin: dosing in renal insufficiency,
- 222 – Drug-drug interaction: aspirin and ACE inhibitor,
- 223 – Warfarin and paracetamol: drug-drug interaction,
- 224 – ACE inhibitor or sartan for diabetic patients with albuminuria,
- 225 – Glimepiride warning in renal insufficiency,
- 226 – LDL-cholesterol concentration in patients with Type 2 diabetes,
- 227 – High BNP or proBNP; untreated congestive heart failure (CHF)?
- 228 – Initial laboratory examinations in patients with congestive heart failure (CHF),
- 229 – Beta blockers in the prevention of gastrointestinal bleeding in patients with cirrhosis,
- 230 – ACE inhibitors or angiotensin-receptor blockers for patients with diabetes and hypertension but no
- 231 microalbuminuria.

232

### 233 *Qualitative integration*

234 The validity of this RCT relies on the actual implementation of MediDSS by physicians in their clinical  
235 activities. Healthcare service studies on CDSSs, however, consistently suggest that the mere provision  
236 of such technology does not guarantee its uptake. In fact, even if a CDSS is readily available within a  
237 hospital, clinicians often fail to follow its recommendations, ignoring in some cases up to 96% of its  
238 alerts [55]. Given this context, our RCT is informed by qualitative interviews aimed to detect the  
239 barriers and facilitators to MediDSS uptake as perceived by diverse health professionals involved in  
240 patient care (e.g., physicians and nurses). The interviews are a part of a larger cross-sectional study,  
241 which involves three Italian hospitals [56]. The interviews will explore variables that may hinder the  
242 use of a CDSS in everyday clinical practice, including technical (e.g., poor usability or knowledge of  
243 system), individual (e.g., negative perception of CDSS or EBM, lack of motivation), group or

244 organizational (e.g., structural or administrative constraints), and cultural factors (e.g., adverse social  
245 norms).

246 When feasible, the trial will be tailored to address the specific needs emerging from the qualitative  
247 assessment. We will collect feedbacks about usability, possible errors, or inaccuracies of the  
248 information and recommendations provided. We will offer the best possible solutions to clinicians and  
249 hospital staff to overcome these problems. We will further organize and facilitate group discussions  
250 among participants to address negative perceptions or misleading beliefs about CDSSs. The qualitative  
251 study seeks to support the use of CDSS by participants, thus increasing the integrity of the intervention  
252 and associated compliance.

253

#### 254 *Study outcomes*

255 Primary outcome: the rate at which the medical problems, which are detected by the MediDSS software  
256 and reported through the reminders, are resolved (i.e. resolution rates).

257 Secondary outcomes: (i) resolution rates for the VTE prevention reminders, (ii) in-hospital all causes  
258 mortality (iii) VTE-related mortality, (iv) in-hospital morbidity for VTE-related causes, and (v) the  
259 length of hospital stay during the study period.

260

#### 261 *Sample size*

262 We calculated the sample size on the basis of the primary outcome. A previous systematic review  
263 assessing the effects of computer reminders delivered to clinicians at the point-of-care on health care  
264 processes and outcomes found a median improvement of 4.2% in process adherence across all reported  
265 process outcomes [57]. Accordingly, assuming resolution rates of 5% in the intervention group versus  
266 3% in the control group due to a possible group contamination, we calculated that a sample of 4,230  
267 reminders will be necessary to detect the difference between the two groups (power = 0.90;  $\alpha$  = 0.05,

two-sided; 1:1 allocation). Because estimates for intracluster correlation are not available, we increased the required sample size (by 10%) to 4,650 reminders to account for clustering by patient. Moreover, based on a prior study evaluating EBMeDS, which recorded an average of 0.30 reminders per individuals triggered at baseline [58], we determined that a total number of 15,500 patients (7,750 per group) need to be enrolled. This figure corresponds to a conservative estimate of the recruitment period of 24 months for the internal medicine departments of the Vimercate Hospital.

### *Allocation and blinding*

Anonymous patient identification (ID) numbers in the EHR system will be the unit of randomization. An individual external to the study group will generate the anonymous IDs using a formula based on patients' unique fiscal code numbers.

We will randomly assign patients to either the control or experimental group with a 1:1 allocation. We will follow a computer generated randomization schedule stratified by gender and age (0–30, 31–60, 61–80, >80 years) using permuted blocks of random sizes [59]. Patients will be randomized immediately after the first launch of their EHR (entry of demographic data by physicians at hospital admission), and the allocation will be maintained through successive admissions.

Patients and study investigators (i.e., researchers, statisticians, information technology specialists, and hospital representatives) will be blinded to the allocation of participants. We will maintain the blinding up to the dataset disclosure. On the other hand, blinding of physicians is not feasible due to the nature of the intervention: the physician will know that a patient has been allocated to the intervention group if an automatic, patient-specific reminder is displayed on the screen.

292    ***Data collection***

293    The data collection for this study will follow the standard data collection procedures of the AODV. We  
294    will collect demographic (i.e., gender, age) and administrative (i.e., anonymous patient ID, admission  
295    and discharge dates, diagnoses) data from the EHR archive on a daily basis. Information on reminders,  
296    including all scripts that have been activated in a patient’s record, will also be collected daily, but  
297    during the night, so as not to disturb or slow down the use of the patient EHR.

298

299    ***Statistical methods***

300    For the primary outcome (i.e., resolution rates), the reminder will serve as the unit of analysis, and the  
301    patient the clustering factor. The patient will be the unit of analysis for the secondary outcomes (i.e.,  
302    length of stay and in-hospital mortality). All analyses will follow the intention-to-treat principle:  
303    patients will be analyzed in the group to which they have been randomized. Descriptive statistics will  
304    be presented as means  $\pm$  standard deviations (SD), medians and interquartile ranges (IQR), or  
305    percentages when appropriate. We will compare continuous variables using the Student’s *t*-test when  
306    normally distributed, and the non-parametric two-sample Wilcoxon rank-sum (Mann-Whitney) test  
307    when they are not normally distributed. We will compare categorical variables using the chi-squared  
308    test or the Fisher’s exact test, as appropriate. To model the resolution rates of the reminders, we will  
309    run a random effects logistic regression analysis, accounting for clustering by patient [60].

310    For hypothesis testing, we will consider a probability level of less than 0.05 as statistically significant.  
311    All statistical tests will be two-sided. We will use the Stata software to perform all statistical analyses  
312    (Stata Corp., College Station, TX, USA).

313

314    ***Data monitoring***

315    Data monitoring will inform the CODES trial conduct, identifying the potential need for adjustments:

316 (i) **Sample size recalculation:** Because the sample size calculation utilizes several assumptions, we will  
317 analyze the first batch of data collected and adjust the estimated sample size, if necessary, at the end of  
318 the sequential roll-out of the intervention. The 24-month recruitment period may also be adjusted,  
319 accordingly.

320 (ii) **Interim analysis:** We will perform an interim-analysis on the primary endpoint after 50% of the  
321 patients have been randomized, after 50% of the expected events have occurred, or after 12 months of  
322 the study's initiation (the assumed half-life of the trial), whichever occurs first. An independent  
323 statistician that is blind to the patient allocation will perform the analysis. This analysis will inform  
324 whether the intervention has been proven for efficacy (beyond reasonable doubt). We will subsequently  
325 decide whether (or not) it is necessary to modify the study or prematurely terminate it, if necessary.

326 (iii) **End of trial:** The end of trial will occur thirty days after the randomization of the last EHR. We  
327 will submit an End of Trial notification and final report to the competent Ethical Committee, the  
328 AODV, and to the Sponsor.

329

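### On the planned 0.30 reminders per patient, the all-patient comparisons of mortality and length of stay are unbiased but strongly diluted; state this and prespecify a supplementary comparison in patients with a generated reminder

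*Protocol*

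**What the plan says.** **Who is randomised.** Every patient admitted to internal medicine is randomised when the record is first opened, before it is known whether any rule will fire (Protocol, Eligibility criteria and recruitment; Allocation and blinding). Allocation carries over to later admissions.

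**How the arms differ.** Only in whether reminders are displayed (Harms). During "the care of control group patients, the generated reminders will not be shown to the physicians, such" that controls receive usual practice (Intervention). All activated scripts are recorded daily (Data collection).

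**How patient-level outcomes are compared.** Statistical methods states: "patient the clustering factor. The patient will be the unit of analysis for the secondary outcomes (i.e" (the sentence goes on to name length of stay and in-hospital mortality). All analyses follow intention to treat, defined as analysis by randomised group. Standard two-group tests are listed. The Protocol names no other patient set.

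**Planning figure.** The number of patients rests on a prior study of the same rule base, "which recorded an average of 0.30 reminders per individuals triggered at baseline" (Sample size). The reference list shows by its title that this study was done in primary healthcare.

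**The concern.** The trial enrols 15,500 patients to obtain 4,650 reminders for its primary outcome, then compares mortality and stay over all 15,500. On the plan's own mean, display of a reminder could not directly reach most of them. Any effect on death or stay among patients with a reminder is averaged with a larger group in which no direct effect is expected.

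At stake is how a null secondary result is read. It could be taken to show that reminders do not affect outcomes, when the comparison had little chance of showing an effect. The design already contains a more sensitive comparison, because hidden reminders are generated and logged in controls. That comparison carries weight only if it is specified before the data are disclosed.

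**Working it through.** **1. Reproduce the plan's figure.** Inputs from Sample size: "Accordingly, assuming resolution rates of 5% in the intervention group versus" "3% in the control group due to a possible group contamination, we calculated that a sample of 4,230" "reminders will be necessary to detect the difference between the two groups (power = 0.90", two-sided 0.05, 1:1.
- Two-proportion formula with continuity correction: 2,115 per group, 4,230 in total. This matches. Without the correction it gives 4,032.
- 4,230 × 1.10 = 4,653, stated as 4,650.
- 4,650 / 0.30 = 15,500 patients, 7,750 per group. This matches.

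**2. Share of patients with a reminder.** For any count, P(at least one) ≤ mean. With mean 0.30:
- at most 0.30 × 15,500 = 4,650 patients (2,325 per group) have a reminder;
- at least 10,850 (70%) have none.

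With Poisson counts, 1 − exp(−0.30) = 0.259 have one, so 74% have none. With overdispersed counts (negative binomial, k from 1 to 0.1), 77% to 87% have none. The bound depends on the mean: at least 50% have none at a mean of 0.5, and there is no bound at a mean of 1.

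**3. Dilution.** Let f be the share with a reminder. With equal baseline risk (assumed), overall RR = (1 − f) + f × RR in patients with a reminder. At f = 0.30:
- RR 0.80: 0.70 + 0.30 × 0.80 = 0.94.
- RR 0.70: 0.70 + 0.30 × 0.70 = 0.91.

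**4. Power at two-sided 0.05.** All patients: 7,750 per group. Patients with a reminder: 2,325 per group (f = 0.30). The Protocol gives no mortality rate, so the rates, risk ratios and equal baseline risk are assumptions.

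| Assumed mortality | RR 0.80: all | RR 0.80: with reminder | RR 0.70: all | RR 0.70: with reminder |
|---|---|---|---|---|
| 3% | 10% | 24% | 17% | 50% |
| 5% | 14% | 38% | 26% | 72% |
| 10% | 24% | 66% | 48% | 96% |
| 15% | 36% | 85% | 67% | 99.6% |

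Length of stay, assumed effect of 0.10 SD in patients with a reminder (0.03 SD overall): 46% against 93%.

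**5. Efficiency gain.** With N patients in total and effect δ in those with a reminder:
- all-patient z = δ f √N / (2 sd_all);
- z among patients with a reminder = δ √(fN) / (2 sd_rem);
- equivalent sample gain = (1/f) × var_all / var_rem.

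Results:
- Equal variance: 1/0.30 = 3.3-fold; 1/0.26 = 3.9-fold; 1/0.80 = 1.25-fold.
- Unequal risk at f = 0.30, mortality 15% with and 5% without a reminder (assumed). Overall mortality is 0.30 × 15% + 0.70 × 5% = 8%. The variances are 0.15 × 0.85 = 0.1275 and 0.08 × 0.92 = 0.0736, ratio 1.73. The gain is 1 / (0.30 × 1.73) = 1.9-fold. Patients with a reminder supply 4.5/8 = 56% of deaths, so RR 0.80 becomes 0.44 + 0.56 × 0.80 = 0.89 overall.

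**6. Is the restricted comparison still randomised?** A patient's first generated reminder precedes any display for that patient. Own allocation therefore should not decide who enters a set defined by that first reminder. Later reminders lack this protection, because earlier displays occurred in one arm only.

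**The case against.** The strongest reply is that the plan contains no error. The all-randomised comparison is unbiased and suits the pragmatic aim: a health system deciding on adoption wants the effect over all admissions, including those in which nothing fires. The outcomes are secondary, no power is claimed for them, and the primary outcome is already confined to generated reminders. A supplementary set could also appear in an analysis plan that is not shown, and the Protocol's wording does not exclude one. All of this stands. It makes the point an improvement to the plan and not a fault in it.

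Four stronger readings are tempting, and the documents do not support them:
- **That 70% of patients can never be exposed.** The 0.30 is a baseline mean from primary care. Here 262 international and 17 local reminders can fire at each record opening, diagnosis, prescription or laboratory result, over successive admissions. Data monitoring provides for the planning assumptions to be rechecked.
- **That the gain is at least 3.3-fold.** This needs equal risk and variance. Patients with a reminder may well be sicker, and the gain then falls.
- **That patients without a reminder receive identical care in both arms.** Strengths and limitations concedes that physicians may carry knowledge between patients. What follows is only that no direct effect of display is expected in them.
- **That any patient with a VTE-prevention reminder can be used for VTE outcomes.** That reminder may fire after others were displayed in the intervention arm only. The priority list includes reminders on antithrombotic selection, and Box 1 makes home anticoagulation an exclusion from prophylaxis. Membership could therefore depend on allocation.

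**Conclusion.** The point holds as a low-cost improvement. On the plan's own mean, at most about 30% of patients would have a reminder, and the all-patient comparisons of mortality and stay would be valid but strongly diluted. How strongly rests on three things the Protocol does not settle: the share of inpatients with a reminder, their baseline risk relative to other patients, and whether any effect is confined to them. Over the cases worked, the gain from the restricted comparison runs from 1.25-fold (80% with a reminder, equal risk) through 1.9-fold (30%, mortality 15% against 5%) to 3.3-fold (30%, equal risk), or 3.9-fold with Poisson counts. A reader might infer that the all-randomised analysis should be replaced. It should not: it remains the main analysis.

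**What to change.** - Keep the all-randomised intention-to-treat comparison as the main analysis of mortality and length of stay.
- State the expected dilution next to it, and update it with the observed share of patients with a reminder when the planning assumptions are rechecked.
- Prespecify a supplementary comparison by randomised arm among patients with at least one generated reminder, shown or hidden. Define entry by the patient's first generated reminder in the trial.
- Report the proportion entering this set in each arm. A difference would warn that entry was not independent of allocation.
- For VTE mortality and morbidity, use the same set, or only patients whose VTE-prevention reminder fired before or together with their first reminder of any kind.

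**Cost.** One additional analysis on data already logged daily, written down before the dataset is disclosed. Its result describes patients with a reminder only and stays secondary to the all-randomised result.
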